**Exploratory outcomes (subcomponents or alternate measures of primary and secondary outcomes)**		
	PrEP uptake	Percentage of participants initiating PrEP *among those not on PrEP at baseline*, self-reported and validated by Ministry of Health records.
	PrEP execution	Percentage of participants with TFVdp levels indicating consistent use *among those reporting current PrEP use.*
	PrEP persistence	Percentage of participants with any detectable TFVdp *among those who ever initiated PrEP.* Participants who self-report discontinuation will be categorized as having undetectable TFVdp levels.
	Recent PrEP use (biomarker)	Percentage of all study participants with biomarker FTCtp^e^ levels indicating consistent PrEP use (≥4 doses per week) for the past 2 wk. Collected at months 6 and 12 only.
	IPV type	Percentage of participants reporting each IPV type (physical, sexual, emotional, and economic) since the last visit, per WHO VAWI [70].

^a^PrEP; preexposure prophylaxis.

^b^TFVdp: tenofovir diphosphate.

^c^IPV: intimate partner violence.

^d^WHO VAWI: World Health Organization’s Violence Against Women instrument.

^e^FTCtp: emtricitabine triphosphate.

The secondary outcomes of the study will be the proportion of participants reporting any IPV and severe IPV (Table 4) between enrollment and month 6, and between month 6 and month 12, and the difference in IPV intensity scores at months 6 and 12. The aim 2 hypothesis is that the proportion of participants reporting any IPV and severe IPV and IPV severity scores will all be *lower* at both time points in the intervention arm versus control arm.

In exploratory analyses, we will first explore effect modification by age (15-19 vs 20-24) and DREAMS participation (current, former, or never) for the primary and secondary outcomes. Second, we will break down the primary outcome into steps along the continuum (PrEP uptake, execution, and persistence) and IPV outcomes by type—physical, sexual, emotional, and economic—to understand where the intervention had its strongest effects. Third, we will compare the proportion of participants per arm with emtricitabine triphosphate (FTCtp) levels indicating consistent PrEP adherence over the past 2 weeks. Comparing TFVdp and FTCtp levels will yield insights on adherence patterns over both a long and short window of time before collection. We will also analyze the alignment of adherence measures with HIV risk perception and behavior to better understand adherence patterns.

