#### Analysis Approach

Descriptive and bivariate statistics will be used to compare participant characteristics in the intervention and control arms and those who completed the study versus those lost to follow-up. Outcomes will be modeled using an intent-to-treat approach with mixed effect logistic and linear regression models. Model predictors will include treatment assignments, randomization strata, and a random effect for ward (cluster) within stratum that is assumed to be independent and normally distributed with mean 0. If the cluster randomization does not adequately balance baseline characteristics across arms, we will conduct exploratory analyses controlling for those characteristics. We will analyze the data from each of the 2 time points separately and the primary outcomes analyses will use a type I error rate of 0.025 at each time point.

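### PrEP execution and persistence are compared between arms in groups whose membership the intervention can change, so these exploratory contrasts cannot show at which step it worked

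*Protocol article*

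**What the plan says.** In the protocol article, the exploratory part of Table 4 splits effective PrEP use into steps.

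- Execution is "Percentage of participants with TFVdp levels indicating consistent use", restricted to participants "among those reporting current PrEP use".
- Persistence is "Percentage of participants with any detectable TFVdp", restricted to participants "among those who ever initiated PrEP". The table adds: "Participants who self-report discontinuation will be categorized as having undetectable TFVdp levels".
- Uptake is restricted to participants not on PrEP at baseline.

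Outcomes and Hypotheses gives the purpose of the breakdown: "to understand where the intervention had its strongest effects". Analysis Approach states: "Outcomes will be modeled using an intent-to-treat approach with mixed effect logistic and linear regression models". The predictors are arm, randomization strata and a ward random effect. No separate approach is given for the exploratory outcomes. Neither that section nor Limitations mentions that two of the denominators can depend on arm.

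**The concern.** Current use at months 6 and 12 arises after the intervention has started. Ever having initiated PrEP does so too, for everyone who had not started before enrollment. The stated objective is to raise uptake as well as adherence, and Eligibility Criteria admits non-users who are interested in PrEP. Arm can therefore change who is counted.

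If the intervention brings in participants who would not otherwise have used PrEP, the users in the intervention arm are a different mix from the users in the control arm. A difference in execution between those two groups combines two things: any real change in pill-taking, and the change in mix. The plan would read the sum as the effect at that step. At stake is the interpretation of the step-by-step breakdown. It could suggest that adherence among users got worse, or better, when no one's adherence had changed.

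**Working it through.** **No plan figure to reproduce.** The article states no rate, power or sample size for execution or persistence. The only related input is in Background: pilot uptake was about twice as high in the intervention arm. All levels below are assumptions.

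**Which denominators can depend on arm (Table 4)**

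| Measure | Denominator | Can arm change it? |
|---|---|---|
| Effective use (primary) | All participants | No |
| Recent use by FTCtp | All participants | No |
| Uptake | Not on PrEP at baseline | No |
| Execution | Reporting current use at the visit | Yes |
| Persistence | Ever initiated | In part: starters before enrollment are also included |

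**Formula.** Let U0 and U1 be the shares using PrEP in control and intervention. Assume that the intervention adds users and removes none. Let e0 be execution in participants who would use PrEP in either arm, the same in both arms, so there is no true effect on them. Let eI be execution in added users.

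- Execution among users, control: e0
- Execution among users, intervention: [U0 × e0 + (U1 − U0) × eI] / U1
- Spurious difference: (1 − U0/U1) × (eI − e0)
- Consistent use over all participants: U0 × e0 versus U0 × e0 + (U1 − U0) × eI

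**Worked case.** U0 = 30%, U1 = 60%, e0 = 40%, eI = 15%.

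- Among users: 40.0% versus (0.30 × 0.40 + 0.30 × 0.15) / 0.60 = 27.5%, a difference of −12.5 points. Check: (1 − 0.5) × (0.15 − 0.40) = −0.125.
- Over all participants: 0.30 × 0.40 = 12.0% versus 0.12 + 0.30 × 0.15 = 16.5%, a difference of +4.5 points.

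**Range with use doubled from 30% to 60%**, e0 of 30-40% and eI of 10-20%.

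- Smallest: 0.5 × (0.20 − 0.30) = −5 points
- Largest: 0.5 × (0.10 − 0.40) = −15 points

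**Other directions.** If eI = e0 the bias is zero. If added users adhere better, it is positive: with e0 = 30% and eI = 40%, 0.5 × 0.10 = +5 points.

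**A real benefit can be hidden.** Take e0 = 30%, eI = 10%, use 30% to 60%, and suppose that the intervention truly raises execution by 5 points in either-arm users. Execution among users is 30% versus (0.30 × 0.35 + 0.30 × 0.10) / 0.60 = 22.5%. Over all participants it is 9% versus 13.5%.

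**Persistence.** The same formula applies with ever-initiators in place of users. Suppose 40% versus 70% ever initiate, with persistence of 40% in either-arm initiators and 20% in added ones. Conditional persistence is 40% versus (0.40 × 0.40 + 0.30 × 0.20) / 0.70 = 31.4%. Over all participants it is 16% versus 22%. The larger the share that started before enrollment, the closer the two arms' initiation rates and the smaller the bias.

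**The case against.** The case for leaving the plan alone is substantial. Both measures are exploratory. No hypothesis, error rate or decision rule is attached to them, and Aim 1 concerns only effective use over all participants. The article states a purpose for the breakdown, not a conclusion that it will draw. All of this limits the weight of the point. It does not remove the bias from contrasts whose denominators Table 4 fixes. The planned adjustment for baseline imbalance does not cure it either, since that responds to differences between the whole arms and not to who becomes a user.

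A reader might infer more than the documents support:

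- **That the pilot predicts a wrong sign.** Background reports that uptake and adherence were both about doubled, with adherence given as device openings on 25% of PrEP days, a measure among users. That runs against an expected negative artefact, although it does not exclude selection.
- **That this breakdown steers scale-up.** The abstract and Conclusions tie that role to the process evaluation, which draws on several other data sources.
- **That persistence is affected as fully as execution.** Starters before enrollment are in its denominator whatever the arm.

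A further fair objection concerns the remedy. All-participant steps are cumulative, so an uptake effect carries through to every later one. In the worked case the +4.5 points arise with no change in either-arm users' execution. All-participant comparisons alone therefore cannot separate uptake from execution. This objection stands, and the fix allows for it.

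**Conclusion.** The point holds, at low to moderate severity. As defined, the execution contrast, and in part the persistence contrast, is open to selection by arm and should not be read as showing where the intervention worked best. The trial's main conclusion is not touched.

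The size rests on assumed rates and on the intervention adding users without removing any. Under doubled use from 30% to 60%, with added users adhering less, the spurious execution difference is −5 to −15 points. Neither the size nor the sign can be known from the documents. It would be wrong to say that the plan will show a false worsening: it can do so, and it can equally show a false gain if added users adhere better.

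**What to change.** 1. Make the randomized arm comparisons over all participants at each step: PrEP use or initiation, any detectable TFVdp, and consistent TFVdp (already the primary outcome). State that these are cumulative and that an uptake effect carries through to later steps.
2. Add execution and persistence comparisons within groups defined by baseline PrEP status (on PrEP, or not on PrEP, at baseline), with every member of the group in the denominator. Among participants on PrEP at baseline, new initiation plays no part, so this comes closest to the question of continued and consistent use.
3. Report execution among current users and persistence among ever-initiators as descriptive figures by arm. Alternatively, give bounds or a sensitivity analysis for participants who would use PrEP under either arm. Do not use them to say where the effect was strongest.

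PrEP history is collected at enrollment and DBS samples at months 6 and 12, and the table already counts self-reported discontinuers as undetectable. The change therefore needs only analysis wording and some extra analysis. The price is that there is no single between-arm execution effect among users, and that precision is lower in the baseline-defined groups.

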#### Analysis Approach

Descriptive and bivariate statistics will be used to compare participant characteristics in the intervention and control arms and those who completed the study versus those lost to follow-up. Outcomes will be modeled using an intent-to-treat approach with mixed effect logistic and linear regression models. Model predictors will include treatment assignments, randomization strata, and a random effect for ward (cluster) within stratum that is assumed to be independent and normally distributed with mean 0. If the cluster randomization does not adequately balance baseline characteristics across arms, we will conduct exploratory analyses controlling for those characteristics. We will analyze the data from each of the 2 time points separately and the primary outcomes analyses will use a type I error rate of 0.025 at each time point.

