#### Data Collection

Data collection visits occur simultaneously in each pair of wards at enrollment, and months 3, 6, and 12 (Table 3). At enrollment, interviewer-administered questionnaires are used to assess sociodemographics, relationship characteristics, IPV, behavioral HIV risk factors, and history of PrEP use. Measures are repeated in follow-up questionnaires to document changes in relevant characteristics, attitudes, and behaviors.

DBS samples are collected via fingerprick at months 6 and 12 from all participants who report initiation or continuation of PrEP since the last visit. For participants who report discontinuation of PrEP, reasons for discontinuation are recorded, but DBSs are not collected. Due to storage and transport challenges, DBS samples are also not collected for participants who have relocated outside the county and have follow-up visits conducted by phone or at a remote location. DBS samples are stored in freezers at the IRDO laboratory and then shipped to the laboratory at the University of North Carolina Center for AIDS Research Clinical Pharmacology and Analytical Chemistry Core for quantification of drug concentrations by liquid chromatography-tandem mass spectrometry technology [60].

**Table 3 table3:** Participant timeline.

Procedures			Month 0 (BL^a^)		Month 1		Month 2		Month 3 (3 MFU^b^)		Month 4		Month 5		Month 6 (6 MFU)		Month 7		Month 8		Month 9		Month 10		Month 11		Month 12 (12 MFU)
Assess and confirm eligibility			✓																								
Informed consent			✓																								
Enrollment			✓																								
Locator information and update			✓						✓						✓						✓						✓

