### Sample Size Considerations

The study is powered to identify an absolute difference of 15% between intervention and control arms for the primary outcomes: the proportion with effective PrEP use at month 6 and month 12. Power calculations are conducted using simulations based on the logistic model with normally distributed ward (cluster) effects and assuming 11 wards per treatment arm with type 1 error of 0.025 to account for separate analyses at each of 2 time points. With 60 participants per ward, we will have ≥80% power to detect a 15% difference in the outcome as long as the SD for ward variation is ≤10% and the level of effective PrEP use in control wards remains <50% (far higher than observed in recent trials and demonstration projects). To allow for up to 20% loss to follow-up, our total sample size will be 1584 participants: 72 adolescent girls and young women in each of the 22 wards (11 wards per arm).

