### Data Analysis: Clinical Trial

#### Outcomes and Hypotheses

The primary outcomes of the study will be the proportion of study participants with effective PrEP use, defined in Table 4, evaluated immediately postintervention, at month 6, and at month 12 to gauge the persistence of intervention effect. TFVdp levels will be dichotomized by Clinical Pharmacology and Analytical Chemistry Core laboratory specialists to delineate between consistent (≥4 doses per week) versus inconsistent (<4 doses per week) adherence [68]. The aim 1 hypothesis is that the proportion of participants with effective PrEP use at (a) month 6 and (b) month 12 will be *higher* in the intervention versus control arm.

**Table 4 table4:** An overview of key measures for the cluster randomized controlled trial, collected at enrollment and months 3, 6, and 12, unless otherwise noted.

Measure		Method

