### Data Analysis: Process Evaluation

#### Quantitative Data

Implementation inputs, processes, and outputs will be analyzed descriptively, and we will draw comparisons across intervention wards. Intervention effects on each mechanism of change will be modeled individually following the approach described for the cRCT. We will regress each mechanism on the exposure (intervention arm assignment), controlling for baseline levels of the mechanism. If the primary analyses show no effect of the intervention on PrEP or IPV outcomes, the results will inform our interpretation of whether the intervention failed to affect the intended mechanism or whether the change in mechanism did not lead to the hypothesized outcome. If the primary analyses suggest a positive intervention effect on PrEP or IPV outcomes, we will conduct causal mediation analysis [72,73]. Coverage, uptake, and exit survey data on perceived impact will also be evaluated as moderators of intervention effectiveness at the site level in exploratory analyses of mechanisms of change.

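### The main IPV models leave out IPV measured at enrollment and admit baseline covariates only in exploratory analyses, which forgoes precision and prespecified protection against chance imbalance

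*Protocol article*

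**What the plan says.** The Analysis Approach section covers primary and secondary outcomes together: "Outcomes will be modeled using an intent-to-treat approach with mixed effect logistic and linear regression models". The predictors follow: "Model predictors will include treatment assignments, randomization strata, and a random effect for ward (cluster) within stratum". IPV prevalence and IPV severity are binary and so take the logistic model; IPV intensity is a continuous score and takes the linear one. Baseline covariates are given a separate, conditional place: "If the cluster randomization does not adequately balance baseline characteristics across arms, we will conduct exploratory analyses controlling for those characteristics". The Limitations section repeats that provision as the answer to baseline differences. The Missing Data section adds covariates only on account of missingness.

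IPV is available at baseline. Under Data Collection for the trial component: "At enrollment, interviewer-administered questionnaires are used to assess sociodemographics, relationship characteristics, IPV, behavioral HIV risk factors, and history of PrEP use". Table 3 ticks IPV history at month 0, and the Table 4 caption says its measures are "collected at enrollment and months 3, 6, and 12, unless otherwise noted", with no exception in the IPV rows.

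The process evaluation follows the trial's modeling approach and adds one element: "We will regress each mechanism on the exposure (intervention arm assignment), controlling for baseline levels of the mechanism".

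**The concern.** Reducing IPV is a named objective and the whole of aim 2. For these outcomes the plan holds the most natural prognostic covariate, the participant's own IPV at enrollment, and keeps it out of the main model. Nothing else in the design balances IPV: the strata are community type and the ward's level of PrEP use.

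Two things are at stake. The first is precision, for outcomes on which the article states no power. The second is how a chance difference in baseline IPV would be handled. The only provision is triggered by observed imbalance, with no stated threshold, and is labeled exploratory. If the adjusted and unadjusted IPV results disagreed, the unadjusted one would remain the main result. The process evaluation shows that the investigators regard baseline adjustment as suitable for repeated questionnaire measures, so extending it to IPV would not be foreign to the plan.

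**Working it through.** **Inputs from the article.** 11 wards per arm ("assuming 11 wards per treatment arm with type 1 error of 0.025"); 60 analyzable participants per ward; 72 enrolled per ward; up to 20% loss; 5 strata; 25% past-year physical IPV in western Kenya (Background). The article gives no ICC, effect size, power or baseline correlation for IPV, so all of these are assumed below and shown as ranges.

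**The plan's own figure.** 60 × 1.2 = 72 per ward, and 72 × 22 = 1584, which reproduces the stated total. It was set for the PrEP outcome and says nothing about IPV. After 20% loss from 72, m = 57.6 per ward remain.

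**IPV intensity (linear model).** With ICC ρ, within-ward correlation r_w and ward-level correlation r_b between baseline and follow-up, the ratio of adjusted to unadjusted variance of the arm effect is

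[ρ(1 − r_b²) + (1 − ρ)(1 − r_w²)/m] / [ρ + (1 − ρ)/m].

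Power starts from a comparison with 80% at two-sided 0.05, using t with 22 − 5 − 1 = 16 df unadjusted and 15 df adjusted.

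*Equal correlation at both levels* (the ratio is 1 − r² whatever the ICC):

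| r | variance ratio | 80% power becomes |
|---|---|---|
| 0.3 | 0.91 | 83% |
| 0.4 | 0.84 | 86% |
| 0.5 | 0.75 | 90% |
| 0.6 | 0.64 | 94% |

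*Baseline explains only within-ward variance* (r_b = 0, r_w 0.3 to 0.6, ICC 0.02 to 0.10). Best case, ICC 0.02 and r_w = 0.6: (0.02 + 0.98 × 0.64/57.6) / (0.02 + 0.98/57.6) = 0.0309/0.0370 = 0.835, power 86%. Worst case, ICC 0.10 and r_w = 0.3: 0.1142/0.1156 = 0.988, power 80%.

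*Strong ward-level correlation* (r_b = 0.8, same ranges): ratio 0.40 to 0.61, power 94% to 99%.

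**Binary IPV.** The r² formula does not apply, so this was simulated: 11 against 11 wards, 58 per ward, a true reduction of about 7 points, two-sided 0.05, 2000 replicates. Ward means were compared by t test before and after residualizing on baseline IPV.

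| ward SD (log odds) | baseline–outcome OR | power unadjusted | power adjusted |
|---|---|---|---|
| 0.2 | 2.7 | 0.698 | 0.769 |
| 0.2 | 4.5 | 0.629 | 0.741 |
| 0.2 | 7.4 | 0.562 | 0.742 |
| 0.4 | 2.7 | 0.396 | 0.503 |
| 0.4 | 4.5 | 0.326 | 0.482 |
| 0.4 | 7.4 | 0.302 | 0.505 |

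The simulation lets the same ward effect drive baseline and follow-up, which favors adjustment. It has no strata and is not the planned mixed logistic model. It shows direction and rough size only.

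**Chance imbalance at baseline.** The SD of the arm difference in prevalence is √{2[s² + p(1 − p)/72]/11}, with ward SD s. For p = 0.25 and s = 0.05: √{2(0.0025 + 0.0026)/11} = 0.0305, so P(|difference| > 5 points) = 10%. With s = 0.03 it is 5% and with s = 0.10 it is 30%. At an assumed p = 0.35 the three values are 7%, 12% and 31%.

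**The case against.** The strongest reply is that this is a condensed article, that a list of what predictors will include need not be exhaustive, and that prognostic covariates for secondary outcomes often appear only in the analysis plan. That would answer a complaint about silence. Here the article is not silent: it says where baseline covariates go, namely into exploratory analyses conditional on imbalance. If the unseen plan already adjusts for baseline IPV, the two texts need to agree.

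Several further points on the other side stand.

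- The plan does provide for baseline differences, so a reader who inferred that enrollment IPV is ignored would go too far. The provision is conditional and exploratory; it does not improve the main estimate.
- A reader might infer that imbalance is likely. The article gives no ward-level variation in IPV, and the assumed range puts a difference above 5 points at 5% to 31%. Plausible is the right word.
- A reader might see a contradiction with the mechanism and mediation models, as if these shared the IPV outcomes. They do not: the listed mechanisms are PrEP self-efficacy and outcome expectations, knowledge, communication, disclosure, stigma and social assets, and no covariates are stated for the mediation analysis. Treating the two sets of models differently is a difference in approach only.
- Converting 1/(1 − r²) = 1.10 to 1.56 into extra participants would mislead. More participants per ward do not shrink the ward component, and the formula does not cover the two binary outcomes.
- In a logistic model the adjusted odds ratio is conditional on baseline IPV and its standard error need not fall; the benefit is in power.
- Table 4 defines IPV as occurring since the last study visit, a window with no meaning at enrollment. The covariate therefore needs a definition before it can be used.

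**Conclusion.** The point holds as one of efficiency and prespecification. The stated IPV models are valid, and the unadjusted comparison is unbiased on average under randomization; the documents do not support reading this as bias. Allocation is revealed to investigators before community mapping, which might suggest arm differences in recruitment beyond chance, but the article does not say whether recruiters know the allocation, so that is not demonstrated.

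What is lost is precision, together with protection fixed before the data are seen. The size is uncertain because every IPV correlation and ICC is assumed. For intensity it runs from almost nothing, when baseline carries no ward-level information, through the 83% to 94% range with equal correlations, to more when the ward-level correlation is high. For the binary outcomes a power gain is expected, but its size is less certain. The point does not reach the primary outcome, whose biomarker is collected only at months 6 and 12 and has no baseline value.

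**What to change.** In the main month 6 and month 12 models for IPV prevalence, severity and intensity, prespecify enrollment IPV as a fixed covariate regardless of observed balance. Use the matching measure for each outcome (the intensity score for intensity, the corresponding binary classification for the other two) and state its baseline recall window. The ward mean of baseline IPV may be added to capture ward-level differences. Keep the unadjusted model as a sensitivity analysis, and say that the adjusted odds ratios for prevalence and severity are conditional on baseline IPV.

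The cost is analysis-plan wording plus the definition of the baseline window; no new data are needed. The article expects data collection to end in May 2026 and results by mid-2027. The change should be recorded before anyone examines IPV outcomes by arm.
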